### Recruitment {15}

Recruitment will be conducted by trained research staff across 30 clusters in Pokhara Metropolitan City. A sampling framework of all individuals between age 40 and 75 years old in Pokhara Metropolitan city will be identified from the publicly available voter list of the Nepal Election Commission (2025). Then they will be stratified by voting centre (total voting centre = 98), sex (male or female), and four age categories (40–48, 49–57, 58–66, 67–75), totalling 784 (=98*2*4) strata. Individuals will be randomly selected within each stratum using computer generated random numbers. Research staff will visit the homes of selected individuals to provide information about the study. If unavailable, staff will attempt to revisit over the subsequent two days. If an individual remains unavailable after three consecutive visits, research staff will skip that household and proceed to the next.

## Assignment of interventions: allocation

### Sequence generation {16a}

Randomization will be conducted at the cluster level, treating wards in Pokhara Metropolitan city as a unit of analysis. Since there are odd number of wards in Pokhara Metropolitan City, three small wards (wards 1, 2, and 3) and two small wards (wards 4 and 5) will be combined respectively, forming a total of 30 clusters (independent 28 wards and 2 combined wards). These total of 30 clusters will be randomly assigned to either the intervention or the control arm in a 1:1 ratio. Randomization of clusters will be performed using stratified permuted block randomization, stratified by population size of wards. Wards with less than 10,000 people, between 10,000 and 30,000 people, and greater than 30,000 people are categorized to small, medium, and large, respectively. Three sequences were created by choosing blocks of size 2 (AB) and 4 (AABB) with equal probability. The resulting blocks were permuted at random and then concatenated.

### Concealment mechanism {16b}

Concealment will be performed by having an independent biostatistician from Johns Hopkins Biostatistics Centre execute randomization, who is not involved in this project.

### Implementation {16c}

Using the allocation sequence developed by an independent biostatistician, 30 clusters will be assigned to either the intervention or the control arm. When research staff recruit a participant from an intervention cluster, the coordinating centre in Nepal will notify a trained FCHV working in the respective cluster, who will visit the home of the participant within a month from the enrollment. The coordinating centre will also subsequently notify a SMS message company in Nepal, so that text messages will be scheduled and sent to the participant between 9–10 am on weekly basis. Research staff will recruit a participant in control clusters with the same approach, where the coordinating centre will notify neither FCHVs nor the SMS company.

## Assignment of interventions: Blinding

### Who will be blinded {17a}

The senior statistician overseeing the project will be blinded. Trial participants and care providers (i.e. FCHVs) will not be blinded due to the nature of the intervention. Investigators and other staffs who support the coordination centres in Nepal on the daily basis, including the PI, will not be blinded.

### Procedure for unblinding if needed {17b}

N/A as the senior statistician is the only one blinded.

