### Trial design {8}

This is an investigator-initiated, pragmatic, superiority, parallel group (1:1), open-label cluster randomized controlled (c-RCT) trial embedded in a type 2 hybrid effectiveness-implementation research study. While the project contains a qualitative study and an implementation study before and after the trial respectively, this paper describes the protocol of the trial only.

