### Strategies to improve adherence to interventions {11c}

To monitor and improve adherence to the intervention, multiple strategies will be implemented. The importance of fidelity will be explained to FCHVs during the training sessions. FCHVs will carry and fill out a paper-based register documenting each home visit. Field supervisors will review these registers regularly for completeness and provide feedback as needed. The data from the registers will be entered into an electronic database developed in REDCap to enable monitoring. In addition, during the midline and endline evaluation at 3 and 6 months, respectively, participants in the intervention arm will be asked the number of FCHV visits they received. These self-reports will be triangulated with FCHV records to assess fidelity and adherence to scheduled visits. These combined strategies will help ensure that the intervention is delivered as intended and allow timely identification of implementation gaps.

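### Field staff who recruit and record outcomes are not masked to ward allocation, and a question put only to intervention participants shows the interviewer the arm

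*Protocol article*

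**What the plan says.** The trial is declared as a "parallel group (1:1), open-label cluster randomized controlled (c-RCT) trial". Item 17a lists who is masked and who is not. On one side, "The senior statistician overseeing the project will be blinded". On the other are participants and FCHVs, because of the nature of the intervention, and the coordinating group: "Investigators and other staffs who support the coordination centres in Nepal on the daily basis, including the PI, will not be blinded". Field research staff appear in neither list. Item 17b settles the matter: "N/A as the senior statistician is the only one blinded".

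On the order of events, item 16c says: "When research staff recruit a participant from an intervention cluster, the coordinating centre in Nepal will notify a trained FCHV working in the respective cluster". For the other arm, "Research staff will recruit a participant in control clusters with the same approach", with no notification following. Item 16b describes concealment only as having an outside biostatistician carry out the randomisation.

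Item 18a has trained research staff enter data on tablets and trains them in BP measurement and questionnaire administration. Item 12 makes SBP change, fasting plasma glucose and 30-day tobacco abstinence (yes/no) the primary outcomes. Item 11c adds that at the 3- and 6-month evaluations "participants in the intervention arm will be asked the number of FCHV visits they received".

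**The concern.** In a ward-randomised trial, anyone who knows the ward's arm knows the arm of every person recruited there. Having an outsider run the randomisation protects the sequence. It does not govern what staff know once wards are labelled and doorstep recruitment begins.

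Two biases are possible. At entry, knowledge of arm can affect how consent is sought and how a borderline screening BP is taken. At follow-up, it can affect BP technique and how an answer about smoking is probed and coded. Intention-to-treat analysis (item 20a) and the per-protocol comparison (item 20c) correct neither.

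The open-label label explains why participants and FCHVs are unmasked. It gives no reason for unmasked data collectors, and item 16c assigns the contact with FCHVs and the SMS company to the coordinating centre. No field task described in the article requires the allocation.

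**Working it through.** **What follows from the text, step by step**

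1. Masking is limited to the senior statistician (17b), so research staff are not masked.
2. Participants are recruited from clusters already called intervention or control (16c), and 16a describes the randomisation sequences in the past tense. Allocation therefore appears to precede recruitment. The wording is not uniform: item 11a times the first FCHV visit from randomisation, 16c from enrolment.
3. Research staff obtain consent (26a), recruit (15), and are trained to measure BP and run the questionnaires (18a).
4. The visit-count question is specified for the intervention arm only (11c). The interviewer or the form must therefore distinguish the arms, and by the 3-month visit at the latest.

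**Exposure of each primary outcome**

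- SBP: exposed, being measured by unmasked staff. The article does not say what device these staff use.
- 30-day abstinence: exposed. It is a yes/no item, and the specimens in item 33 are tested for HbA1c, lipids and fasting plasma glucose, with no biochemical test of smoking listed. It is apparently self-reported.
- Fasting plasma glucose: a laboratory value, largely unaffected.

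**Scale for SBP.** Inputs from item 14: SD 15.46, ICC 0.01, cluster-size COV 0.65, 15 clusters of 23 per arm (345 analysed), alpha 0.05/3 taken as two-sided (critical value 2.394).

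- Design effect = 1 + ((1 + 0.65²) × 23 − 1) × 0.01 = 1.317.
- SE of the difference = 15.46 × √(2 × 1.317 / 345) = 1.35 mmHg.
- Check on the plan: 5/1.35 − 2.394 = 1.31, which gives 90.4% power. The stated 90% is reproduced.

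Now suppose there is no true effect, but the recorded change differs between arms by b because of knowledge of arm. The values of b are assumptions; none comes from the document.

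| b (mmHg) | share of 5 mmHg target | false-positive rate (nominal 1.7%) |
|---|---|---|
| 1 | 20% | about 5% |
| 2 | 40% | about 18% |
| 3 | 60% | about 43% |

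**Scale for smoking.** Inputs from item 14: 15 clusters of 30 per arm, control quit proportion 0.019, difference 0.05, ICC 0.01.

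- Design effect = 1 + 29 × 0.01 = 1.29; effective n = 450/1.29 = 349 per arm.
- Check on the plan: 0.019 against 0.069 gives 79.7% power. The stated 80% is reproduced.
- Expected quitters: 450 × 0.019 = 8.6 in control and 450 × 0.069 = 31 in intervention.
- If 2% of intervention smokers who have not quit were wrongly recorded as quit, that would be 0.02 × 0.981 × 450, or about 9 people. With no true effect, the false-positive rate would be about 20%. For 1% and 3% it would be about 6% and 40%. These fractions are also assumptions.

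**The case against.** The best defence is that the trial is openly pragmatic and open-label and already constrains its staff. Item 15 draws candidates at random from the voter list within 784 strata and drops a person after three visits. Item 10 sets numeric thresholds on averaged readings, on two occasions for hypertension, and adds laboratory criteria for diabetes. Item 16c requires the same recruitment approach in control wards, and item 18a trains staff in verbatim questioning and monitors entries daily. The primary contrast is a change from baseline, so a constant baseline shift from selection would largely cancel. All of this stands, and it narrows the entry problem to consent and the taking of BP near the threshold. It does not protect follow-up BP technique or smoking classification.

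A second defence also stands: masking at ward level leaks. FCHVs in intervention wards attend a 5-day training (item 11a), and once they start visiting, the ward's arm is known locally. Releasing allocation participant by participant would therefore not conceal it.

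A reader might infer more than the article supports:

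- **Recruiters choose who is approached.** They do not; item 15 selects at random.
- **The same individuals recruit and later assess.** The article names only a category, research staff.
- **Staff are told the arm, or abstinence is declared to be self-reported.** No sentence says either. The first follows from 17b and 11c; the second is inferred from the absence of any listed biochemical test.
- **A bias of known size is present.** Nothing in the document estimates one.

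**Conclusion.** The point holds as a stated design choice, not as a gap left by a condensed article: 17b confines masking to one statistician, and 11c puts an arm-revealing question to one arm only. SBP and 30-day abstinence are exposed to knowledge of arm at measurement, and consent and BP screening are exposed at entry. Fasting plasma glucose is largely spared.

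The magnitude is unknown. The 20% to 60% of the SBP target, and the false-positive rates shown with it, are conditional on an assumed 1 to 3 mmHg differential in recorded change. They also use the plan's SD and ICC as given. They show that modest shifts would matter against targets of this size, and do not show that such shifts will occur. The conclusion also rests on reading 16c as placing allocation before recruitment, which the differing visit timings in 11a and 16c leave less than fully explicit. The change is worth making because it is cheap, but it should not be presented as achieving full masking.

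**What to change.** 1. State in 17a that research staff who screen, obtain consent and collect outcomes are not told ward allocation, and correct 17b to match.
2. In REDCap, restrict allocation to the coordinating-centre staff who notify FCHVs and the SMS company.
3. Where feasible, complete consent and baseline in a ward before its FCHVs are activated, within the visit window the protocol already sets. The two descriptions of that window (11a from randomisation, 16c from enrolment) need to be reconciled first.
4. Ask the FCHV-visit question in both arms at 3 and 6 months, as the last item, after BP and smoking have been saved. Asked of controls, it also measures contamination.
5. Acknowledge residual unmasking as a limitation.

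The cost is access rights, the order of one form and some wording, with no extra staff. Step 3 may constrain field scheduling. The downside is incomplete protection. Staff may still learn a ward's arm from FCHVs, residents or participants during recruitment and follow-up, and one participant's answer to the visit question can reveal the arm for the next participant in that ward. The bias is reduced and not removed.

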## Data collection and management

### Plans for assessment and collection of outcomes {18a}

In the trial, data will be collected at three time points: baseline (0 months), interim (3 months), and endline (6 months). The types of data collected and its specific timeline has been presented earlier. In addition to data for primary and secondary outcomes, we will collect data for intervention adherence, which will be used for sensitivity analysis. To maintain data quality, several procedures will be undertaken. First, data collection will be entirely digitalized to minimize data entry errors. Trained research staff will enter data directly into the REDCap application on tablets provided by the coordinating center. Each morning, the tablets will be distributed to the research staff, and all devices will be collected back at the end of the day, when staff in coordinating centers will check the condition of tablets and update the operating systems if needed. Data entered by research staff will be monitored daily by the data management team, which is comprised of data managers in the coordinating center and one data manager in Johns Hopkins Bloomberg School of Public Health. Any duplications, missing values, or other data entry errors will be reported to a senior staff member at the coordinating center, who will address the issues by communicating with the field research staff and, when necessary, the investigators. Second, research staff will be trained for data collection techniques through 7-day training prior to the field placement, during which they will be trained on the use of REDCap, verbatim questionnaire administrations, and clinical assessment techniques (e.g. BP measurements, finger prick glucose measurement, height, weight).

Study instruments will be pre-tested with population living outside of the study site to ensure clarity, user-friendliness, and consistency in interpretation among participants.

### Plans to promote participant retention and complete follow-up {18b}

To promote participant retention, research staff will make a phone call to participants the day before each follow-up visit to remind them of the scheduled visit. If there is a participant drop out, we will identify the reason why (i.e. deaths, participant withdrew informed consent, migration) and compare the baseline characteristics of those who dropped out vs retained in the study to explore the extent of the selection bias. For those remained in the study but deviated from the intervention protocol, all outcome data will be collected and used for sensitivity analysis (i.e. exploratory per-protocol analysis)

### Data management {19}

Data will be stored in Johns Hopkins University (JHU) REDCap, which is HIPPA compliant and approved by the Johns Hopkins Bloomberg School of public Health (JHSPH) Institutional Review Boards (IRB). Only authorized personnel with username and password can access the JHU REDCap database, and each of their access will be logged and recorded to maintain accountability. All personally identifiable data will be deleted before data transfer, and the original dataset (i.e., containing personally identifiable data) will be erased five years after the study’s completion. Tablets used for data collection will be encrypted while the data is on storage devices. These devices will be routinely updated with security patches. Measures to maintain data quality is described earlier.

### Confidentiality {27}

As addressed earlier, personally identifiable information of enrolled participants will be stored on encrypted devices. Only authorized personnel will have access to the JHU REDCap database, whose access will be recorded. All identifiable information will be de-identified before sharing or publication.

### Plans for collection, laboratory evaluation and storage of biological specimens for genetic or molecular analysis in this trial/future use {33}

Laboratory technicians certified in Nepal will collect 5 mL of venous blood sample at the baseline and endline from all participants. HbA1c and lipid panels (total cholesterol, LDL cholesterol, HDL cholesterol, and triglyceride) will be assessed for all participants while fasting plasma glucose will be additionally measured for those who had fasting fingerprick glucose ≥100 mg/dL. All samples will be analyzed following the reference method approved by the International Federation of Clinical Chemistry and Laboratory Medicine (IFCC). All specimens will be properly disposed of after completion of tests. No genetic or molecular analyses are planned for this trial or any ancillary studies.

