### Outcomes {12}

Primary outcomes are mean change SBP (mmHg), fasting plasma glucose (mg/dL), and 30 days tobacco abstinence (yes/no). Secondary outcomes will include change in mean diastolic blood pressure (mmHg), blood pressure control (<140/90 mmHg) (yes/no), HbA1c (%), weight (kg), total cholesterol (mg/dL), high-density lipoprotein (HDL) cholesterol (mg/dL), low-density lipoprotein (LDL) cholesterol (mg/dL), total glycerides (mg/dL), adherence to antihypertensive medicines (yes/no), adherence to hypoglycaemic medicines (yes/no), Fagerstrom Test for Nicotine Dependence (FTND) score, 7-days tobacco abstinence (yes/no), harmful alcohol consumption (yes/no), low salt intake (yes/no), high physical activity (yes/no), high fruits and vegetable intake (yes/no).

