## Statistical methods

### Statistical methods for primary and secondary outcomes {20a}

The primary analysis will follow an intention-to-treat approach, comparing the mean differences in changes in systolic blood pressure, fasting plasma glucose levels, and changes in smoking status between individuals assigned to the intervention arm vs control arms. Primary outcomes will be measured at baseline and six months, requiring models that account for repeated measures and the hierarchical structure of participants nested within sites. To compare changes between groups, we will use mixed-effects models for each outcome: linear mixed-effects models for continuous outcomes (SBP, fasting blood glucose) and a mixed-effects logistic regression for the binary outcome (smoking status), each including a random intercept for participants. Fixed effects will include intervention, time (baseline and 6 months), their interaction, and potential confounders. For continuous outcomes, the interaction term represents the difference in mean change between groups. For the binary outcome, it represents the difference in change in log-odds of smoking cessation, with the odds ratio indicating how much greater (or smaller) the change in odds of cessation is for the intervention group relative to control.

Although outcomes may be correlated, the univariate approach is conservative and simplifies interpretation without assuming a multivariate distribution. Sensitivity analyses will use multivariate models accounting for correlations between outcomes. Continuous outcomes will be analyzed jointly using repeated-measures MANOVA or a multivariate linear mixed model with an unstructured covariance matrix. For mixed outcome types, a multivariate logistic mixed model or joint modeling approach will be applied. These models account for both outcome correlations and data hierarchy, allowing estimation of overall intervention effects and assessment of robustness relative to univariate analyses.

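### The finger-prick gate on the fasting plasma glucose assay is not limited to baseline; if applied at endline it withholds a primary outcome from participants with the lowest glucose and pulls the effect toward zero

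*Protocol article*

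**What the plan says.** The section on biological specimens {33} is the only place in the article that says who receives an FPG assay. Laboratory technicians "will collect 5 mL of venous blood sample at the baseline and endline from all participants". HbA1c and lipids "will be assessed for all participants while fasting plasma glucose will be additionally measured" under a condition: "fasting plasma glucose will be additionally measured for those who had fasting fingerprick glucose ≥100 mg/dL". The condition carries no time point, and the sentence on the draws names both baseline and endline. The section adds that specimens are disposed of once the tests are complete.

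Outcomes {12} reads: "Primary outcomes are mean change SBP (mmHg), fasting plasma glucose (mg/dL), and 30 days tobacco abstinence (yes/no". Statistical methods {20a} says "Primary outcomes will be measured at baseline and six months" and "The primary analysis will follow an intention-to-treat approach", using mixed models with arm, time and their interaction.

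Eligibility criteria {10} defines diabetes by a fasting finger-prick of at least 100 mg/dL, FPG of at least 126 mg/dL and HbA1c of at least 6.5%, and excludes FPG above 250 mg/dL. The missing-data section {20c} offers complete-case versus imputation comparisons as sensitivity analyses when more than 5% of a variable is missing.

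**The concern.** As a screening step the gate is sensible. As an endline rule it would make measurement of a primary outcome depend on the level of that outcome. A participant with diabetes at baseline whose endline finger-prick is below 100 mg/dL would have blood drawn but no FPG result. If the intervention lowers glucose, more such participants fall in the intervention arm, so the remaining values understate the difference. The planned model does not include the endline finger-prick and would not correct for this. Because specimens are discarded after testing, the missing values could not be recovered later, whatever the analysis plan says.

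**Working it through.** **1. The plan's own sample size.** Inputs from Sample size {14}: difference 26 mg/dL, SD 45.5, ICC 0.01, COV of cluster size 0.65, 15 clusters of 6 per arm, alpha 0.05/3, power 90%. Two-sided testing is assumed.

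- Individual n per arm = 2(2.394 + 1.282)² × (45.5/26)² = 82.75.
- Design effect = 1 + ((0.65² + 1) × 6 − 1) × 0.01 = 1.0754.
- Required: 82.75 × 1.0754 = 89.0 per arm, against 90 stated. Power at 90 per arm is 0.904.

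The stated figure reproduces, with FPG observed in everyone analysed.

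**2. The gate at baseline.** The diabetes definition already contains finger-prick ≥100 mg/dL, so the gate removes nobody from the glucose analysis.

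**3. The gate at endline, closed form.** Suppose endline FPG is normal with SD 45.5 and is seen only if ≥100. With a = (100 − mean)/45.5, the proportion lost is Φ(a) and the observed mean is mean + 45.5 × φ(a)/(1 − Φ(a)). For an assumed control endline mean of 170:

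- Control: a = −1.538, 6.2% lost, observed mean 175.9.
- Intervention (mean 144): a = −0.967, 16.7% lost, observed mean 157.6.
- Observed difference −18.3 instead of −26.

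For control endline means of 150 to 190 the observed difference runs from −15.0 to −21.3.

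**4. The gate at endline, simulated on the finger-prick.** Baseline FPG is truncated to 126–250 (from eligibility). Endline SD is 45.5 and the effect −26. Assumed, because the document does not give them: baseline mean, baseline–endline correlation 0.3–0.7, and finger-prick error SD 10. Endline FPG is missing when the finger-prick is below 100.

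Power = Φ(|d| / (s√(DE/n₀ + DE/n₁)) − 2.394), where n₀ and n₁ are 90 less the loss, d is the baseline-conditional estimate, and s is either 45.5 or the SD of the observed values.

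| Baseline mean | Lost, control | Lost, intervention | Estimate | Power, SD 45.5 | Power, observed SD |
|---|---|---|---|---|---|
| 154 | 11–12% | 27–28% | −16.4 to −18.4 | 0.38–0.47 | 0.60–0.64 |
| 171 | 6% | 17% | −18.9 to −21.4 | 0.55–0.64 | 0.72–0.78 |
| 189 | 3% | 9% | −21.5 to −23.3 | 0.72–0.77 | 0.82–0.86 |

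The estimate column spans the complete-case change and the baseline-conditional estimate. Example at baseline mean 171 and correlation 0.5: n₀ = 90 × 0.937 = 84.3, n₁ = 90 × 0.831 = 74.8, d = 19.5, s = 38.8. The standard error is 6.39, so power = Φ(3.05 − 2.39) = 0.74. Repeat runs move the ends of the ranges by about a point (control loss down to 2%, power with SD 45.5 up to 0.78).

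**5. When nothing goes wrong.** With a true effect of zero, loss is equal (6.2% and 6.3%) and there is no bias. If only the baseline finger-prick counts, there is no loss and no bias.

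**The case against.** The strongest reply is that the text does not say a new finger-prick at endline decides the assay. The past-tense wording of the gate can mean those who were positive at screening, since the same 100 mg/dL cut opens the diabetes definition. Statistical methods {20a} states six-month measurement without conditions, the study timeline (Figure 3) is not shown, and this is one condensed sentence in an article. This stands in part. A reader might infer that endline FPG will be lost and the effect underestimated; the document does not settle that. What remains is that the only rule on the assay covers both draws and leaves the damaging reading open.

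Three further inferences go too far.

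- That the best responders are lost. Those lost have the lowest endline values: a fall from 240 to 130 stays in, while a fall from 127 to 98 is likely to drop out.
- That no imputation can repair the loss. The gate is a separate measurement. If the endline finger-prick is recorded, regression imputation on it returned −25.8 to −26.2 for a true −26, assuming the relation stays linear below 100 mg/dL. The planned model does not use it, and the article names no such imputation.
- That power falls to about 40–62%. That figure pairs a shrunken difference with the full SD of 45.5, although truncation also narrows the observed SD.

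**Conclusion.** The point holds as a conditional one. The assay rule, followed as written at endline, can withhold a primary outcome according to its own level, and this conflicts with the intention-to-treat analysis of change to six months. If it is applied that way and the true effect is −26 mg/dL, about 9–28% of the intervention arm and 2–12% of control lose FPG. The estimate shrinks to about −16 to −23. Power is about 0.60–0.86 with the observed SD, or 0.38–0.78 with SD 45.5, against the planned 0.90.

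These sizes rest on assumed baseline means of about 154–189 mg/dL and correlation 0.3–0.7; the direction does not, provided there is a true benefit. Since unassayed samples cannot be recovered, the wording should be settled before endline sampling starts.

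**What to change.** In the biological specimens section {33}, restrict the ≥100 mg/dL finger-prick gate to baseline screening. State that at endline FPG is assayed on the venous sample of every participant who met the diabetes definition at baseline, whatever the endline finger-prick value. The design in Sample size {14} then stands as calculated.

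The cost is one sentence in the laboratory procedure and some additional FPG assays on blood that is already drawn. No extra visit or draw is needed.
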